### Research objectives and hypotheses

The trial has three main objectives:To test the clinical efficacy of the therapy compared to supportive counselling (SC).To determine preliminary estimates of cost-effectiveness of the AVATAR therapy.To explore explanatory mechanisms of action as well as moderators for AVATAR therapy.

The trial hypotheses are:AVATAR therapy will be more effective in reducing the frequency and severity of auditory hallucinations, in comparison to SC.AVATAR therapy will be more effective in reducing the reported omnipotence and malevolence of auditory hallucinations, in comparison to SC.The improvements attributable to AVATAR therapy will be maintained at 24 weeks follow-up.AVATAR therapy will be more cost-effective than SC.The mediators of treatment effects for AVATAR therapy on changes in auditory hallucinations will be beliefs about voices (specifically omnipotence and malevolence), beliefs about the self (improved self-esteem), appraisal of voice relationship (specifically relative power and assertiveness), and reduction in anxiety.

The moderators of the treatment effects for AVATAR therapy will be number of voices, type of content (derogatory versus non-derogatory), ratings of the created voice/image, beliefs about problems and social support.

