After completing the creation of the avatar (introductory session), the therapy is delivered in 6 weekly 45-minute sessions of which up to 20 minutes involves face-to-face work with the avatar and the remaining time is spent with the therapist and participant in direct contact both assessing current voices and planning the AVATAR session and subsequently debriefing on it. The number and progress of sessions is determined by a discussion with the participant at each session concerning any change in severity, content, malevolence or frequency of the hallucinations. Therapy will be terminated before six sessions if the participant has reported complete absence of any voices for at least three consecutive sessions. The total number of sessions can be extended by up to three further sessions where there is a clear rationale for the likely benefit of additional sessions, such as evidence of delayed and ongoing improvements during later sessions, on self-reported severity, content, malevolence or frequency of the voice (any additional sessions are agreed by consensus within the therapy team). Evidence of any adverse reactions will result in completion of an adverse events form (see safety assessment section below). Evidence of any adverse reactions to therapy will be closely monitored. Therapy will be terminated in the event of any significant deterioration in mental state which renders the continuation of therapy inadvisable (for example where the therapy sessions are associated with significant increased distress and/or risk of harm to self/others); and any such termination would be decided through agreement between therapist (in consultation with the AVATAR therapy team), the participant and the relevant clinical team. All therapists delivering AVATAR therapy have at least 5 years of clinical experience in psychosis and have been trained by [name] on delivery of the therapy.

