### Supportive counselling

The control condition comprises a manual-based, face-to-face, SC approach based on the manual used in the SOCRATES clinical trial [27] to control for non-specific elements of therapy exposure. It will be delivered over the same number and duration of sessions (including application of the same rules for early termination and extension as above), with the aim of matching the duration of total therapist contact time to that in the AVATAR arm.

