### Measures

The primary outcome measure of the study is the total score on the auditory hallucinations subscale of the Psychotic Symptoms Rating Scale (PSYRATS-AH [28]) at the 12-week follow-up. It is an interviewer-assessed measure of the frequency and duration of auditory hallucinations over an average week. The PSYRATS is specifically designed for use with people suffering from psychosis, with inter-rater reliability ranging from 0.79 to 1.00 and high validity when compared with similar psychiatric scales [28]. It has been extensively used in research with these populations and has been shown to be acceptable to service users.

Secondary outcome measures will include the Revised version of the Beliefs about Voices Questionnaire (BAVQ-R, [29]: a self-report measure which focuses on the patient’s beliefs about the voices, and indexes how likely the voices are to affect behaviour. In addition to the total score, changes in two subscales will be analysed: omnipotence and malevolence.

Other standardised measures will be used to assess changes in voice experience and appraisals: the Voice Acceptance and Action Scale: VAAS [30] and Voice Power Differential Scale: VPDS [10]. We will assess changes in delusions using the Psychotic Symptoms Rating Scale: PSYRATS-D [28] and other psychotic symptoms using the Scale for Assessment of Positive and Negative Symptoms: SAPS and SANS [31]. Other standardised questionnaires will assess anxiety and depression (Depression Anxiety and Stress Scale: DASS-21 [32]; (Calgary Depression Scale [33]); self-esteem [34]; quality of life (Short Assessment of Quality of Life, MANSA [35]); and illicit drug use [36].

In order to assess progress during the therapy, the PSYRATS-AH [28] and the VPDS [10] will be completed by the therapist and the participant at each therapy session. Additionally, an adapted version of the Sense of Presence Questionnaire [37], the State Social Paranoia Scale [38] in relation to the avatar along with analogical scales will be used to assess the participant’s interaction with the avatar and the match obtained during the creation of the image/voice. Burns Empathy Scale [39] will be completed in sessions 2, 4 and 6. All the questionnaires in the study are being delivered in paper-and-pencil format.

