### Analysis

#### Statistical analysis

Analysis will be conducted in Stata version 13 (StataCorp, College Station, TX, USA) [40]. Descriptive statistics within each randomised group will be presented for baseline values. These will include counts and percentages for binary and categorical variables and means and standard deviations, or medians with lower and upper quartiles, for continuous variables, along with minimum and maximum values and counts of missing values. There will be no tests of statistical significance or confidence intervals for differences between randomised groups on any baseline variable.

The primary hypothesis for change in the severity of auditory hallucinations as measured by the total PSYRATS-AH score will be analysed using a mixed (random) effects model allowing for the baseline measurement of PSYRATS-AH and treatment assignment as fixed effects, at 12 weeks. This takes account of missing outcomes assuming a missing at random mechanism which allows missingness to depend on baseline severity of AH and treatment assignment. Therapist effects will be modelled by including a random effect for each therapist in the two therapy conditions. The use of a mixed (random) effect models will allow for estimation of the intra-cluster correlation coefficient, a measure of the proportion of variance in outcome because of therapist effects, which can be used in future applications; no estimate of this is currently available. Secondary outcome measures will be analysed using the same modelling approach. This includes analysis of the primary outcome and secondary outcomes at 24 weeks.

A secondary mediation analysis will investigate putative mediational factors (including beliefs about voices, self-esteem, anxiety/levels of distress) using modern causal inference methods. This involves using parametric regression models to test for mediation of the AVATAR therapy on AH through the putative mediators. Analyses will adjust for baseline measures of the mediator, outcomes, and possible measured confounders. We will include repeated measurement of mediators and outcomes to account for classical measurement error and baseline confounding, and instrumental variable methods (baseline covariate by randomisation interactions as potential instruments) to investigate the sensitivity of the estimates to these problems and that of unmeasured confounding [41].

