Moderators will be assessed separately by repeating the primary analysis models and including interaction terms between the randomised intervention and each moderator. The coefficient of the interaction term is a measure of whether the treatment effect differs between levels of the moderator.

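### The avatar match rating cannot be tested as a moderator by interaction with randomised arm, because only AVATAR participants have one

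*Protocol article*

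**What the plan says.** The Research objectives and hypotheses section lists the expected moderators of the treatment effect. Number of voices comes first, followed by "type of content (derogatory versus non-derogatory), ratings of the created voice/image, beliefs about problems and social support". The Background, at the end of the Pilot study section, also puts forward the rating of the created voice and image as a possible moderator.

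The last paragraph of the Statistical analysis section fixes the method for all of them: "Moderators will be assessed separately by repeating the primary analysis models and including interaction terms between the randomised intervention and each moderator". It also fixes how the result is to be read: "The coefficient of the interaction term is a measure of whether the treatment effect differs between levels of the moderator". The base model is the primary one, "allowing for the baseline measurement of PSYRATS-AH and treatment assignment as fixed effects, at 12 weeks", with a random effect for therapist.

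Four other sections show where the rating comes from:
- **Measures:** analogue scales record "the match obtained during the creation of the image/voice".
- **AVATAR therapy:** building the avatar is the opening step of that treatment. "After completing the creation of the avatar (introductory session), the therapy is delivered in 6 weekly 45-minute sessions".
- **Supportive counselling:** "The control condition comprises a manual-based, face-to-face, SC approach", with no avatar described.
- **Planned interventions:** counselling participants are offered AVATAR therapy only once the trial is over.

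**The concern.** A moderator of a between-arm effect needs a value in both arms, because the question is whether the AVATAR-minus-counselling difference changes along it. This rating is produced by one of the treatments, so the other arm has nothing to compare at a given level of it. It is also recorded after randomisation, so it is not a baseline characteristic even among AVATAR participants.

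What is at stake is the meaning of one reported result. Participants who rate the match highly may also have a better prognosis or stronger expectations. An association between rating and outcome within the AVATAR arm cannot separate that from a true effect of match quality. Under the article's own interpretation sentence, such an association would carry the label of effect modification.

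**Working it through.** There is no stated figure to reproduce. The question is whether the planned coefficient can be estimated.

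**Inputs**
- About 71 participants per arm and 142 in total, with a 20% allowance for loss (Sample size).
- Primary model terms: baseline PSYRATS-AH and arm (Statistical analysis).
- Added terms: the moderator and its interaction with arm (Statistical analysis, last paragraph).
- Rating available in the AVATAR arm only, after randomisation (AVATAR therapy; Supportive counselling; Planned interventions; Measures). The baseline assessment precedes randomisation (Assessments and follow-up), so it cannot supply the rating.

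**Model**

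Let T = 1 for AVATAR and 0 for counselling, B = baseline PSYRATS-AH, R = rating. The fixed part is

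E[Y] = b0 + b1·B + b2·T + b3·R + b4·T·R

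The treatment effect at rating r is b2 + b4·r, so b4 is the coefficient that the article interprets. The slope on R is b3 + b4 in the AVATAR arm and b3 in the counselling arm. To isolate b4, both slopes must be known.

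**Three cases**, using the rank of the five-column design matrix with simulated covariates and 71 per arm:

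1. *Counselling ratings missing, complete cases.* Only the 71 AVATAR participants remain. T equals 1 throughout, so it duplicates the intercept, and T·R equals R. Rank 3 of 5. No treatment effect is left in the model to be moderated.
2. *Counselling ratings set to a constant c.* Then R = T·R + c·(1 − T) holds exactly for everyone. With c = 0 the interaction column equals the rating column. With any other c the dependency runs through intercept, arm, rating and interaction together. Rank 4 of 5 for both values tried (0 and 5). Only the sum b3 + b4 can be estimated. If software drops the rating main effect, the term printed as the interaction is the within-AVATAR slope.
3. *Moderator observed in both arms.* Rank 5 of 5, and b4 can be estimated.

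**What this means for interpretation.** Suppose the AVATAR-arm slope is s. Pure prognosis (b3 = s, b4 = 0) and pure moderation (b3 = 0, b4 = s) imply the same data in the AVATAR arm, and no counselling data distinguish them. The therapist random effect does not change this, since it alters the variance structure and not the fixed-effect columns.

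**Who could contribute.** With the planned loss, 71 × 0.8 = 56.8, about 57 AVATAR participants, and 0 from counselling. A moderator measured in both arms would use 142 × 0.8 = 113.6, about 114. These counts give scale only. The rank deficiency is the same at any sample size.

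**The case against.** The case on the other side has four parts.

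**The analysis is exploratory.** The Abstract places moderators among the secondary objectives, and the Pilot study section says only that the rating may play this role. This stands and sets the severity. A reader might infer that the efficacy analysis or the whole moderator plan is compromised. The documents do not support that: the primary model does not contain the rating, and the other four moderators are features that participants in either arm can have before treatment.

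**The failure would be visible.** With the counselling ratings missing, the arm and interaction terms drop out and the statistician would notice. This also stands. A reader might infer that the trial will publish a within-arm association as effect modification. That would happen only if a constant were filled in or a one-arm slope were mislabelled, and the article proposes neither.

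**Other provisions might cover it.** The Abstract promises modern causal methods for the mediation and moderator work, and an analysis plan not shown may treat this variable separately. But the Statistical analysis section states only the interaction model for moderators, "including interaction terms between the randomised intervention and each moderator", without exception. This is a stated rule that cannot be carried out for one named variable, not a detail left for later. The missing-at-random provision does not help either. It concerns missing outcomes, whereas here a covariate is undefined for a whole arm. Imputing it would make the answer depend on the imputation assumption.

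**Counselling participants could rate an avatar later.** They may receive AVATAR therapy after the trial, but nothing plans to use ratings from that stage. On a plain reading of the timing, such ratings would follow the outcomes and come only from those who take up the offer.

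**Conclusion.** The point holds. For the avatar rating, the prescribed arm-by-moderator interaction is not identified, and the reading that the article attaches to its coefficient is not available. At most, the data support an association between rating and outcome within the AVATAR arm, from about 57 participants after planned loss.

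The scope is one of five hypothesised moderators in a secondary, exploratory analysis, so the severity is moderate to minor. The primary analysis and the other four moderators are unaffected.

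The conclusion rests on one inference: that no counselling participant has a rating when the outcomes are analysed. The article does not say so outright. It follows from the descriptions of the two treatments, the timing of the baseline assessment and the content of the rating, and nothing in the article contradicts it.

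**What to change.** 1. In the Pilot study section and in Research objectives and hypotheses, stop describing the rating as a moderator of the AVATAR-versus-counselling effect.
2. In the last paragraph of Statistical analysis, restrict the interaction models to moderators measured before randomisation in both arms.
3. Add a sentence on the rating. Suggested wording: 'Within the AVATAR arm only, 12-week PSYRATS-AH will be regressed on the avatar match rating, adjusting for baseline PSYRATS-AH. This is an exploratory within-arm association and does not test whether the treatment effect varies with the rating.'
4. If a moderation claim is wanted, name a causal method instead and state its assumptions. One option is principal stratification using baseline predictors of the rating. It would rest on assumptions that the trial data cannot fully check.

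The cost is wording only, with no new data collection. One hypothesis is reduced to a within-arm association.

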## Methods/Design

The study design is a single blind randomised controlled trial. Patients who meet inclusion criteria (see below) will be independently randomised to receive either 7 sessions of AVATAR therapy or SC (see Fig. 1). Both groups will continue to receive standard psychiatric care. Written consent will be obtained from each eligible participant prior to assessment and randomisation. Participants will be allocated to conditions using randomised permuted blocks (with a block size randomly varying between 2 and 6). The block sizes will not be disclosed to ensure allocation concealment. Randomisation will be carried out at the point of consent through an independent web-based service provided by the UKCRC Registered Clinical Trials Unit (CTU) at King’s College London (Registration Number 053). The randomisation will be conducted by the CTU in order to keep the data management and the statistician blind to the study condition. Assessments will be conducted by research assessors blind to therapy allocation. In case of unblinding, the trial coordinator will switch assessors for follow-up assessments. The reliability of the raters on the assessment battery will be formally assessed. For reporting the trial, the Consolidated Standards of Reporting Trials (CONSORT) with the extension for non-pharmacologic treatment and the Recommendations for Interventional Trials (SPIRIT) guidelines will be followed [25]. All data collected and study-related information will be stored securely at the Institute of Psychiatry, Psychology and Neuroscience, King’s College, London.

### Participants

The inclusion criteria are as follows: 1) aged over 18 years; 2) have experienced troubling auditory hallucinations for at least 12 months; 3) primary diagnosis of non-organic psychosis (including *International Classification of Diseases* (ICD)-10 categories F20-29 and F30-39, subcategories with psychotic symptoms). Criteria for exclusion are as follows: 1) unable to give informed consent; 2) currently in receipt of cognitive behaviour therapy for psychosis or attending a group specific to hearing voices; 3) unable to identify a single dominant voice to work on; 4) refusing all medication; 5) a diagnosis of organic brain disease; 6) a primary substance dependency; 7) auditory hallucinations in a language not spoken by the therapists; 8) a command of spoken English inadequate for engaging in therapy; 9) inability to tolerate the assessment process.

Clinical staff will be informed of the study and basic criteria for inclusion and asked to refer patients who express an interest in taking part. Patients are also able to self-refer in response to information given to primary care centres and in response to posters in the relevant clinical areas of the Trust. The majority of the referrals will be received from the South London and Maudsley National Health Service (NHS) Foundation Trust. However, for the patients who are not currently within South London and Maudsley (SLaM) services, we will follow Patient Identification Centre (PICs: Health Boards or Trusts, which can identify possible participants for the study) activity procedure. Finally, other clinicians working in Mental Health Services in the UK who are aware of the study via clinical contacts or conferences conducted by the research team can also refer participants. All referrals will be screened for eligibility. Participants’ diagnosis will be confirmed by an independent experienced and trained psychiatrist examining medical case notes and using the OPCRIT system [26].

### Planned interventions

Eligible participants will be randomised to either the AVATAR therapy or SC arm of the trial. AVATAR therapy and SC will both be delivered over 7 (1 introductory session plus 6 therapy) sessions lasting approximately 45 minutes. Both therapies will be manualised and trial therapists provided with training and on-going supervision. Therapy sessions will be audio-recorded and assessed for therapy competence and adherence to the treatment model. Participants allocated to SC will have the opportunity to receive AVATAR therapy at the end of the trial.

### AVATAR therapy

Participants first create a computerised representation of the person or entity that they feel represents the source of their voices (see Fig. 2). Over the following sessions the therapist facilitates a direct dialogue between the person and the avatar they have created, in which the therapist voices the avatar’s speech. The system is set up in two rooms in the same building with two linked computers. Participants sit in one room facing the monitor on which the avatar appears. The therapist sits in a second room facing the monitor with a control panel that allows them to talk to the participant in their own voice or in the morphed avatar voice. The therapist can see and hear everything that is appearing on the participant’s monitor as well as the participant’s responses, adjusting therapeutic interventions and response to the avatar according to the unfolding dialogue. Should the participant be distressed at any point they can press a button on the desk that will terminate the session, replacing the on-screen avatar with a pleasant scene. The therapist also uses his/her judgement to anticipate distress and modify the avatar interaction accordingly. For more details on the software used in AVATAR therapy please see Leff et al. [19].

After completing the creation of the avatar (introductory session), the therapy is delivered in 6 weekly 45-minute sessions of which up to 20 minutes involves face-to-face work with the avatar and the remaining time is spent with the therapist and participant in direct contact both assessing current voices and planning the AVATAR session and subsequently debriefing on it. The number and progress of sessions is determined by a discussion with the participant at each session concerning any change in severity, content, malevolence or frequency of the hallucinations. Therapy will be terminated before six sessions if the participant has reported complete absence of any voices for at least three consecutive sessions. The total number of sessions can be extended by up to three further sessions where there is a clear rationale for the likely benefit of additional sessions, such as evidence of delayed and ongoing improvements during later sessions, on self-reported severity, content, malevolence or frequency of the voice (any additional sessions are agreed by consensus within the therapy team). Evidence of any adverse reactions will result in completion of an adverse events form (see safety assessment section below). Evidence of any adverse reactions to therapy will be closely monitored. Therapy will be terminated in the event of any significant deterioration in mental state which renders the continuation of therapy inadvisable (for example where the therapy sessions are associated with significant increased distress and/or risk of harm to self/others); and any such termination would be decided through agreement between therapist (in consultation with the AVATAR therapy team), the participant and the relevant clinical team. All therapists delivering AVATAR therapy have at least 5 years of clinical experience in psychosis and have been trained by [name] on delivery of the therapy.

